### Blinding

The therapist and patients will not be blinded because of the nature of the intervention, but it is feasible to make the researchers, outcome evaluators, and statisticians blinded to the group/treatment assignment. Furthermore, the outcome evaluation will be done by well-trained personnel in order to minimize bias. After the completion of data analysis, the statistician will present un-blinded data to the researchers.

### Date management and monitoring

All staff members will be trained to ensure data quality. The researchers will record data in case report forms (CRFs) and any changes to a CRF will be signed and dated. Data administrators will enter data into the computer. Data of the subjects will be stored at the security site. The collected data will be identified by a coded ID number. Data collected during the research will be confidential and only accessed by the researchers. The corresponding author will also have access to the dataset. The original data will be kept in the research center and will be accessible upon reasonable request. Moreover, the anonymous data will be shared with other researchers. The results of the trial will be disseminated through journal publication regardless of the magnitude of the effects.

The Ethics Committee of Shanghai Sixth People’s Hospital will be fully aware of the trials from the first draft of the protocol to the end of the research process and will monitor the accuracy of the trials. The research team will organize a conference to discuss problems encountered and propose solutions every month. The Data Monitoring Committee was not involved in the current trial considering the low-risk intervention.

### Safety monitoring

Patients will be informed of the potential risks and benefits of the trial and sign an informed consent form before participating in the research to protect their rights and interests.

Intervention involved in the study protocol is exercise therapy, so serious adverse events are rare. When potential adverse events occur in a patient, the researchers will record the severity, duration, treatment measures, and event outcomes. The doctor will determine the causal relationship between the treatment and the adverse event and decide whether the patient is suitable for continued participation in the study. Also, relevant information will be reported to the ethics committee.

The following are the criteria for terminating a patient from the study: (1) a serious adverse event happened that the researchers believes that the patient is not suitable for continued participation or the patient has requested to be withdrawn from the study; (2) the patient is found to have serious diseases during the study; (3) the patient has received other treatments that may affect the outcomes.

### Statistical analysis

In this trial, we will implement the intention-to-treat analysis and statistical analysis will be carried out by a researcher not involved in the evaluation and treatment. Data will be recorded in the CRFs. Data analysis will be done using the SPSS version 26.0 statistical software. In order to incorporate the data of the participants into data analysis regardless of the protocol adherence, all the analyses will be performed in accordance with the intention-to-treat principle. Data will be expressed as frequencies and percentages for categorical variables, mean, and (±) standard deviation for continuous variables. Intergroup comparison of the type of SD will be calculated using chi-squared test. Intergroup comparison of pain, ROM, scapula position (LSST, SI, PMI), and patients’ satisfaction with shoulder function will be calculated using repeated measurement ANOVA. Intergroup comparison of time points will be calculated using Least Significant Difference. Statistical significance is defined as a *P* value of < 0.05.

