### Outcome assessments

All outcome assessments will be evaluated by well-trained personnel who are blind to the treatment allocation. Assessments will be performed at baseline, 2-, 4-, and 6-week treatment, and at the 6-week follow-up after the end of treatment.

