### Sample size calculation

The study is designed to achieve 95% power overall at the 0.05 significance level to detect change on the CMS between groups after 6 weeks. According to G*Power 3.1 software, we use repeated measurement analysis of variance (ANOVA) (Effect size = 0.25, Number of measurements = 4) to calculate the sample size. Considering a dropout rate of 20%, a sample size of 90 (45 per group) will be needed in this trial.

The statistical hypotheses are:
H0: mean CMS scale (scapular stabilization exercise) = mean CMS scale (traditional rehabilitation training).HA: mean CMS scale (scapular stabilization exercise) ≠ mean CMS scale (traditional rehabilitation training).

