### Randomization and allocation concealment

Consented eligible participants will be randomly allocated to one of the two groups in a ratio of 1:1. Patients’ allocations will be according to a computer-generated randomization table. Generation of the allocation sequence, enrollment of participants, and assignment of participants to interventions will be done by the main researcher of the trial. When the subject is enrolled into the study, the subject will be assigned a study number sequentially. If the subject drops out of the study, the assigned study number will not be reused. The block size will not be known until the end of the study for allocation concealment. The random numbers will be sealed in envelopes by an individual other than the trial researchers. The envelopes will be randomly selected by the patients, and they would be assigned to the intervention or control groups according to the contents of the envelope.

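### The named repeated-measures ANOVA drops patients with a missing visit, so unless values are imputed first, about 18 of 90 leave an analysis called intention-to-treat

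*Protocol article*

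**What the plan says.** The Statistical analysis section fixes the population and the method together. On the population it states that "all the analyses will be performed in accordance with the intention-to-treat principle", with the declared aim of counting participants whether or not they adhered. On the method, pain, range of motion, the three scapula position measures and "satisfaction with shoulder function will be calculated using repeated measurement ANOVA", with SPSS 26.0 as the software. Type of scapular dyskinesis is compared by a chi-squared test. No test is named there for CMS, but the Sample size calculation section plans the CMS comparison as a repeated-measures ANOVA ("Effect size = 0.25, Number of measurements = 4").

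Four other places bear on the point:

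- Outcome assessments: "Assessments will be performed at baseline, 2-, 4-, and 6-week treatment, and at the 6-week follow-up after the end of treatment".
- Sample size calculation: "Considering a dropout rate of 20%, a sample size of 90 (45 per group) will be needed in this trial".
- Exit criteria and Safety monitoring: patients who cannot adhere, are lost to follow-up or receive other treatments that may affect outcomes leave the study.
- Study design: participants are asked whether their data may be used if they withdraw.

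The article does not mention imputation, a mixed model or any other way of using an incomplete record.

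**The concern.** Classical repeated-measures ANOVA, as run by the standard SPSS routine (GLM Repeated Measures), needs a value at every visit entered. A patient who lacks one is deleted entirely, including the scores already collected. The patients most likely to have incomplete records are those who stop adhering or leave. These are the patients whom the intention-to-treat statement sets out to keep, and whose data the consent form asks permission to use.

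What is at stake is the validity of the comparison. Patients and therapist are unblinded (Blinding) and the exercises are done at home (Interventions), so dropout that depends on progress and differs between arms is plausible. A comparison of patients with complete records would then no longer be protected by randomisation, yet it would be reported as intention-to-treat.

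**Working it through.** **Inputs from the article.** N = 90, 45 per group; dropout 20%; f = 0.25; 4 measurements; power 95%; alpha 0.05 (Sample size calculation). Five assessments (Outcome assessments). The article does not say which visits enter the ANOVA.

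**Inputs assumed.** Between-visit correlation 0.6, normally distributed scores, dropout by arm, and rates of isolated missed visits. The article gives none of these.

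**1. The plan's own figure.** For the group-by-time test the noncentrality is f² × N × m / (1 − ρ), with 3 and 3(N − 2) degrees of freedom. With m = 4 and ρ = 0, 95% power needs N = 72 (noncentrality 0.0625 × 72 × 4 = 18), and 72 / 0.8 = 90, the stated figure. The article states neither the correlation nor which F test was used. The between-group test with ρ = 0.1 gives 70, or 88 after inflation, which is also close. Either way, 90 corresponds to about 72 evaluable patients.

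**2. Patients left out.** 90 × 0.20 = 18 dropped; 90 − 18 = 72 analysed.

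**3. Isolated missed visits.** If the 72 who stay each miss any of the four post-baseline visits with probability q, complete records number 72 × (1 − q)⁴:

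- q = 1%: 72 × 0.99⁴ ≈ 69
- q = 5%: 72 × 0.95⁴ = 72 × 0.815 ≈ 59

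**4. Possible bias.** Suppose the fraction p of an arm with the lowest week-4 scores leaves, and the week-4 to week-6 correlation is ρ. The completers' week-6 mean in that arm is then raised by ρ × φ(z_p) / (1 − p), in SD units, where φ is the standard normal density and z_p its p-quantile. With ρ = 0.6:

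| p | φ(z_p) / (1 − p) | shift in arm (SD) |
|---|---|---|
| 0.10 | 0.1755 / 0.90 = 0.1950 | 0.1170 |
| 0.15 | 0.2332 / 0.85 = 0.2743 | 0.1646 |
| 0.20 | 0.2800 / 0.80 = 0.3500 | 0.2100 |
| 0.25 | 0.3178 / 0.75 = 0.4237 | 0.2542 |
| 0.30 | 0.3477 / 0.70 = 0.4967 | 0.2980 |

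The bias in the group difference is the difference between the two arms' shifts:

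- 20% vs 20%: 0.2100 − 0.2100 = 0
- 25% vs 15%: 0.2542 − 0.1646 ≈ 0.09 SD
- 30% vs 10%: 0.2980 − 0.1170 ≈ 0.18 SD
- 20% vs 0%: 0.2100 − 0 = 0.21 SD (overall dropout here is 10%, not 20%)

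**5. Scale.** Read as a two-group contrast, f = 0.25 is d = 2 × 0.25 = 0.5 SD. The three unequal cases are therefore 0.09 / 0.5 = 18%, 0.18 / 0.5 = 36% and 0.21 / 0.5 = 42% of the planned effect. The bias favours the arm that loses more of its low scorers.

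**The case against.** The case against has real force on several points.

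- A reader might infer that the intention-to-treat statement and the ANOVA cannot both be carried out. That goes too far. Multiple imputation followed by the same ANOVA would reconcile them, and an analysis plan not shown here could specify it. What stands is that the article positively names a method that deletes incomplete cases by default, beside a claim covering all analyses. Followed as written, it gives a complete-case result.
- A reader might infer that the primary CMS result is certainly affected. The Statistical analysis section does not list CMS among the ANOVA outcomes; the link comes only from the sample size method. For the listed continuous secondary outcomes it is explicit.
- Not every analysis is affected in this way. In the chi-squared comparison of dyskinesis type, patients are lost visit by visit rather than from the whole analysis.
- A reader might infer that the trial loses its planned power. The 20% inflation already covers the expected loss in numbers, though not any further loss from isolated missed visits.
- The bias figures rest on a strict dropout rule and on unequal dropout by arm. The article gives one overall rate and no difference between arms, and with the same mechanism and rate in both arms the figure is zero. The documents therefore support a risk of bias, not a statement that the result is biased.
- The article ties its intention-to-treat aim to adherence rather than to missed visits. But patients who cannot adhere exit the study, so non-adherence and missing visits largely coincide.
- A mixed model does not recover data never collected. The Exit criteria do not say whether assessments continue after exit.

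**Conclusion.** The point holds in limited form. Unless values are imputed first, the named method would leave out about 18 of 90 randomised patients at the planned dropout, and a complete-case comparison would be labelled intention-to-treat. This is explicit for pain, range of motion, scapula position and satisfaction, and inferred for CMS. The 18 rests on a planning allowance, so the actual loss may differ.

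The main harm is possible selection bias: about zero if dropout works the same way in both arms, and about 0.09 to 0.21 SD under the assumed unequal, outcome-related dropout, against a planned effect of about 0.5 SD. These are illustrations of size, not predictions. The point is more than an omitted detail, because the article fixes a method that does not deliver its stated population, and a better one is available in the same software.

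**What to change.** In the Statistical analysis section, name a likelihood-based linear mixed model for repeated measures (SPSS MIXED) for CMS and the continuous secondary outcomes. Include group, visit, group-by-visit and baseline score, and use all available post-baseline visits of all randomised patients in their allocated arm. Add one prespecified sensitivity analysis for data not missing at random, such as imputation that shifts missing experimental-arm values in the unfavourable direction. Report the complete-case ANOVA only as supportive.

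The cost is a little more analysis work; sample size, visits and software stay as they are. The Trial status section says that amendments will be posted in the trial registry, so the change can be recorded there before unblinding. Two limits should be stated with it: patients with no post-baseline score still contribute no outcome data, and the mixed model is valid only if dropout depends on observed data.

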On the other hand, the scapula plays an important role in maintaining complex shoulder kinematics [6]. Altered scapular motion and position have been termed scapular dyskinesis (SD) [7]. Kibler et al. [8] classified SD into 4 types. Type-1 represents the dorsal prominence of the inferior angle of the scapula. Type-2 represents the dorsal prominence of the entire medial border. Type-3 represents the elevated superior border of the scapula, and the scapula could also be anteriorly displaced from the posterior thorax. Type-4 represents the symmetry of bilateral scapula. According to data reported in the literature, SD may be important risk factors for periarthritis of the shoulder [9–11]. The scapular muscle group, consisting of the trapezius, serratus anterior (SA), pectoralis minor (PM), levator scapulae (LS), rhomboid muscle (RM), and teres major (TM), is mainly responsible for scapular movement and dynamic stabilization of the scapula. An optimal interaction between these muscles is needed to provide stability and mobility of the scapula both at rest and during shoulder movements [11]. Previous studies have reported excessive activation of upper trapezius (UT), PM, LS, TM, and decreased activity of middle/lower trapezius (MT/LT), SA, RM in subjects with SD, and different types of SD have different manifestations of muscle imbalance [12–17]. These altered muscle activation patterns are associated with altered scapular kinematics, including reduced scapular upward rotation, external rotation and posterior tilt [12]. Overall, SD is closely related to muscle imbalance and is usually associated with shoulder pathology [18]. However, it is unclear if SD is the cause or the result of shoulder pathology.

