Turgut et al. (2017) [21]	30 subacromial impingement syndrome patients	Wall slides with squat, wall push-ups plus ipsilateral leg extension, lawnmower with diagonal squat, resisted scapular retraction with contralateral 1-leg squat, and robbery with squat.	Three-dimensional kinematics, the Turkish version of the Shoulder Pain and Disability Index (SPADI).	Scapular stabilization exercise therapy is an effective tool for controlling pain and improving disability status.
Hotta et al. (2018) [22]	50 patients with shoulder impingement	The neuromuscular exercises were towel slide, PNF scapular, inferior glide, and scapular clock. The strengthening exercises were diagonal D1, push-up plus, full can, prone horizontal abduction with external rotation from 90° to 135°, side-lying external rotation with abduction at 0°, diagonal D2 eccentric, scapular punch, and horizontal rowing.	Resting position and scapular kinematics, muscular strength, numeric pain rating scale, Shoulder Pain and Disability Index (SPADI).	Motor control and muscular strengthening training improve function among subjects with shoulder impingement syndrome.

In the present study design, we developed a randomized controlled trial to evaluate the effect of scapular stabilization exercise based on the type of SD in patients with periarthritis of the shoulder. We hypothesized that scapular stabilization exercise based on the type of SD would improve shoulder function and correct SD better than traditional rehabilitation training.

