### Inclusion criteria

Males and females aged 20 to 60 years old.Unilateral shoulder pain, with or without limited shoulder movement.Patients who meet the diagnostic criteria with broadly defined periarthritis of the shoulder, including rotator cuff injuries, biceps tendonitis, supraspinatus tendonitis, shoulder impingement syndrome, and shoulder instability.A maximum pain score of equal or less than 5/10 on a numerical rating scale (NRS)Patients volunteered to participate in the study and signed informed consent.

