#### Secondary outcome measures

The secondary outcome measures include pain degree, ROM, type of SD, scapula position, and patients’ satisfaction with shoulder joint function. The Lateral Scapular Slide Test (LSST), the Scapular Index (SI), and the Pectoralis Minor Index (PMI) are used to assess scapula position.

Pain intensity at rest, during movement, and sleeping at night are assessed using the numerical rating scale (NRS), with 0 being “No pain,” and 10 being “The worst pain” [34]. The NRS has been shown to be a reliable and valid instrument for the assessment of pain intensity [35, 36]. For the ROM assessment, the electronic goniometer is used to measure active flexion and abduction movements and passive flexion and abduction movements. Previous studies have revealed the electronic goniometer have good validity and reliability [37].

The type of SD is assessed by the comprehensive method combined visual observation and palpation [38]. Subjects are evaluated at rest position in a warm and comfortable environment. Raters make the initial assessment by visual observation, and then put hands on the subject’s bilateral scapula for further identification. This method shows satisfactory inter-reliability [35]. The subjects are assessed by three raters with previous experience with assessments of SD, and raters are allowed discussions to derive a unanimous decision. Subjects whose scapular pattern could not be identified by raters or assessment results are inconsistent among raters will be excluded.

LSST is a quantitative method for assessing inferior angle displacement and recognizing scapular symmetry [39]. The distance from the inferior angle of the scapula to the corresponding thoracic spinous process is measured in three positions: the first position is of the arm relaxed at the sides; the second is hands placed on the lateral iliac crest; and the third is 90° of shoulder abduction and in full internal rotation. A difference of more than 1.5 cm between two sides is considered asymmetric.

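### The chi-squared test on scapular dyskinesis type is valid for any difference in type mix but is not specific to correction, which is what the trial hypothesises

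*Protocol article*

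**What the plan says.** All references are to the Protocol article.

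- **Hypothesis.** Background ends by hypothesising that the type-based exercise "would improve shoulder function and correct SD better than traditional rehabilitation training".
- **Scale.** Background reports a scheme that "classified SD into 4 types". Types 1 to 3 are each described by an abnormal prominence or displacement and are given no order. For the last, "Type-4 represents the symmetry of bilateral scapula".
- **Status and timing.** "The secondary outcome measures include pain degree, ROM, type of SD, scapula position, and patients’ satisfaction with shoulder joint function". The visits are set under Outcome assessments: "Assessments will be performed at baseline, 2-, 4-, and 6-week treatment, and at the 6-week follow-up after the end of treatment". Baseline type is therefore on record.
- **Analysis.** For this outcome, Statistical analysis gives one sentence: "Intergroup comparison of the type of SD will be calculated using chi-squared test". It names the type itself as the variable and mentions no correction, baseline type or visit.
- **Entry.** The criterion closest to shoulder status is "Unilateral shoulder pain, with or without limited shoulder movement". No inclusion or exclusion criterion requires an abnormal type, although the Interventions section lists exercises for types 1 to 3 only.

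**The concern.** Correction has a direction: a patient starts with an abnormal type and ends symmetric. A chi-squared test on a nominal variable has none. Its statistic is unchanged if the type labels are permuted, so type 4 counts the same as any other category.

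Two things follow. A significant result may reflect a different mix of types 1, 2 and 3 with equal correction in both arms. And a patient who was symmetric throughout looks the same as one who was corrected. The P value would then be attached to a claim, better correction of SD, that it does not test specifically. The exercises differ by type, so unequal movement among the abnormal types is a realistic possibility.

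**Working it through.** **The plan's own figure.** The documents size the trial only for the Constant-Murley score (CMS): "The study is designed to achieve 95% power overall at the 0.05 significance level to detect change on the CMS between groups after 6 weeks". The total of 90 is reproduced by a repeated-measures ANOVA (within-between interaction, f = 0.25, 4 measurements), if the correlation between measurements is assumed to be 0: N = 72, and 72 / 0.8 = 90. It says nothing about SD type. It does supply the arm sizes used below: 45 randomised per arm, or 45 × 0.8 = 36 after the planned 20% dropout.

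**Inputs.** Four categories give a 2 × 4 table with 3 df if all types occur. Two-sided alpha is 0.05. The documents give no type frequencies or correction rates, so all rates below are assumptions. Type 4 is read as the corrected state because it is the only type described as symmetric.

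**Formula.** With n per arm, category proportions a and b in the two arms and m = (a + b)/2, the noncentrality is λ = n × Σ[((a − m)² + (b − m)²)/m]. Power is the upper tail of the noncentral chi-squared distribution beyond the 5% critical value, with 3 df for type and 1 df for type 4 yes/no.

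**1. Equal correction, abnormal types exchanged.** Types 1/2/3/4 are 30/30/10/30% against 10/30/30/30%. Only types 1 and 3 contribute, each with m = 0.20 and a deviation of 0.10: Σ = 2 × (2 × 0.01/0.20) = 0.20.
- 36 per arm: λ = 7.2, rejection probability 0.60.
- 45 per arm: λ = 9.0, rejection probability 0.71.

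The proportion in type 4 is identical in the two arms.

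**2. Correction spread over types 1 to 3.** The uncorrected patients have the same split over types 1 to 3 in both arms. Take type 4 at 20% vs 50%: the type 4 term is 2 × 0.0225/0.35 = 0.1286, and the rest gives 2 × 0.0225/0.65 = 0.0692, so Σ = 0.1978 and λ = 36 × 0.1978 = 7.12. Both tests have the same λ. They differ only in df.

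| Type 4, control vs exercise | 36 per arm: 3 df / 1 df | 45 per arm: 3 df / 1 df |
|---|---|---|
| 10% vs 30% | 0.40 / 0.56 | 0.49 / 0.66 |
| 15% vs 40% | 0.49 / 0.66 | 0.59 / 0.76 |
| 20% vs 40% | 0.31 / 0.46 | 0.38 / 0.54 |
| 20% vs 50% | 0.60 / 0.76 | 0.71 / 0.85 |
| 30% vs 50% | 0.27 / 0.41 | 0.34 / 0.49 |
| 30% vs 60% | 0.56 / 0.73 | 0.67 / 0.82 |

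Before rounding, the shortfall runs from 13.5 to 17.0 points.

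**3. Only one type corrected.** Take 27/27/26/20% against 7/27/26/40%. For type: Σ = 2 × 0.01/0.17 + 2 × 0.01/0.30 = 0.1843, so λ = 6.64 at 36 per arm. For type 4 yes/no: Σ = 2 × 0.01/0.30 + 2 × 0.01/0.70 = 0.0952, so λ = 3.43. Power is 0.56 vs 0.46 at 36 per arm and 0.67 vs 0.54 at 45, now in favour of the 3-df test.

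**4. Role of baseline type (simulation, 4,000 runs).**
- No difference between arms, 20% type 4 at baseline: the 2 × 4 test rejects in 0.050 (36 per arm) and 0.048 (45 per arm) of runs.
- Correction 20% vs 50%, 20% type 4 at baseline, 36 per arm: 0.37 for the 2 × 4 test, 0.53 for type 4 yes/no, 0.66 for Mantel-Haenszel stratified by baseline type.
- The same correction rates with no type 4 at baseline: 0.61, 0.79 and 0.77, so stratifying adds nothing there.

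**The case against.** The strongest reply is that the sentence fixes no coding, degrees of freedom or visit. A corrected/not-corrected comparison is also a chi-squared test, and a condensed article may leave the coding to a full analysis plan that is not shown. This stands as far as the 2 × 4 form is a reading and not a quotation. But the variable named is the type, which the article defines with four categories, and nothing points to a two-category coding or to baseline type.

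Three stronger conclusions are tempting, and the documents do not support them.

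- **That the test always loses power.** It does when correction is spread over types 1 to 3. The order reverses when correction sits in one type, which is plausible because the exercises differ by type. The documents give no rates to settle it.
- **That ignoring baseline makes the test biased.** Allocation is randomised 1:1, so chance imbalance is already covered by the error rate, as the simulation shows.
- **That the SD part of the hypothesis goes unanswered.** Type is one of several secondary outcomes. The Lateral Scapular Slide Test, Scapular Index and Pectoralis Minor Index also bear on scapular position, and each has its own planned analysis. Percentages are planned for categorical data, so a reader could see the type 4 proportion beside the P value. The formal hypotheses and the sample size concern the CMS only.

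What remains is that the P value itself would not be specific to correction.

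**Conclusion.** The point holds in a limited form. The stated test is valid for any difference in type distribution, but it does not separate correction from a shift among abnormal types, and it leaves recorded baseline information unused. Under the assumed exchange of types 1 and 3, it would reject in 60% to 71% of trials with equal correction in both arms. Its power against a corrected yes/no comparison may be about 14 to 17 points lower or, in the one-type scenario, 10 to 13 points higher. Leaving out baseline type costs interpretability and, if patients with type 4 at baseline are enrolled, efficiency. It does not cost validity.

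These sizes rest on assumed rates and on reading type 4 as the corrected state. The primary CMS conclusion is unaffected. The change is still worth making, because it is cheap and aligns the analysis with the stated hypothesis.

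**What to change.** Replace the sentence on SD type with a definition and a matching test:

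- Define correction as type 4 at week 6 among patients with type 1, 2 or 3 at baseline.
- Compare arms by a Mantel-Haenszel test stratified by baseline type, or by logistic regression with baseline type as covariate. Report the risk difference with its 95% CI.
- Keep the full table of type by arm and visit as descriptive.
- Secondary outcome measures excludes subjects whose pattern cannot be identified or on whom raters disagree, without saying at which visit. State that this applies at baseline only, so that randomised patients stay in the intention-to-treat analysis. Count later unclassified results as not corrected, with a sensitivity analysis of that choice.

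This costs wording only, because the data are already collected. There are two small losses: shifts among types 1 to 3 are no longer tested, and any patient with type 4 at baseline leaves this comparison. With 20% type 4 at baseline, about 36 × 0.8 = 29 per arm would remain. The simulated Mantel-Haenszel power of 0.66 already reflects that loss, because a stratum in which every patient is type 4 at week 6 adds nothing to the statistic.

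### The planned repeated-measures ANOVA makes no use of the collected baseline value and does not say which effect answers the week-6 question; a baseline-adjusted week-6 comparison would usually be more powerful at almost no cost

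*Protocol article*

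**What the plan says.** The Statistical analysis section gives the method for the continuous secondary outcomes: "Intergroup comparison of pain, ROM, scapula position (LSST, SI, PMI), and patients’ satisfaction with shoulder function will be calculated using repeated measurement ANOVA". It then plans between-group comparisons at time points by Least Significant Difference (LSD). It names no covariate, does not list the visits that enter the ANOVA, and does not say whether the group main effect or the group-by-time interaction carries the conclusion. CMS, the primary outcome, is not in that list.

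For CMS the method has to be read from the Sample size calculation section, where repeated-measures ANOVA is the basis ("Effect size = 0.25, Number of measurements = 4") and the aim is "to detect change on the CMS between groups after 6 weeks". The null hypothesis there is worded "H0: mean CMS scale (scapular stabilization exercise) = mean CMS scale (traditional rehabilitation training", and the alternative is its two-sided counterpart. Neither names a time point.

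The Outcome assessments section lists five visits: "Assessments will be performed at baseline, 2-, 4-, and 6-week treatment, and at the 6-week follow-up after the end of treatment". The baseline value is therefore available for every outcome.

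**The concern.** The power statement asks about a difference between groups after 6 weeks. The method named offers three tests that could be taken as the answer, and none uses baseline efficiently.

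- **Group main effect.** If baseline is one of the levels, this compares averages over visits that include a pre-treatment one. Randomisation makes the expected difference there zero, so the visit dilutes the contrast. Early visits dilute it further if the effect builds up slowly.
- **Group-by-time interaction.** Its null hypothesis is parallel profiles. It can reject because of a passing difference at weeks 2 and 4 when the groups are equal at week 6.
- **LSD comparison at week 6.** This addresses the right time point, but nothing indicates that it is adjusted for baseline.

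If the four measurements are instead the post-baseline visits, baseline drops out of the comparison altogether. In each case a collected predictor is left unused in a trial expecting about 36 evaluable patients per arm. A real benefit at the end of treatment could be missed, or the conclusion could rest on a test that does not speak to week 6.

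**Working it through.** **Inputs from the protocol.** Two-sided alpha 0.05, power 95%, effect size f = 0.25, 4 measurements, 20% dropout, 90 patients (Sample size calculation); 1:1 allocation (Randomization and allocation concealment); five visits (Outcome assessments). Evaluable patients: 90 × 0.8 = 72, or 36 per arm.

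**Inputs that the protocol does not give, so assumed.** Equal correlation ρ between visits (0.3 to 0.7), unit SD at each visit, the time course of the effect, and the week-6 difference d in SD units (0.5 to 0.8).

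**Step 1: the protocol's own figure.** For a within or interaction test, λ = f²·N·m/(1 − ρ), with m − 1 and (N − 2)(m − 1) degrees of freedom. With f = 0.25, m = 4 and ρ = 0, N = 72 gives λ = 0.0625 × 72 × 4 = 18 and power 95.6%; 72/0.8 = 90, an exact match. For the between-group main effect, λ = f²·N·m/(1 + (m − 1)ρ). That needs 132 at ρ = 0.5 (165 with dropout), and comes near 90 only at ρ of about 0.1 (70, or 88 with dropout). The stated total therefore fits an interaction or within test better than a group main effect, but only through a correlation that the protocol does not state.

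**Step 2: power of each reading.** Take 36 per arm, ρ = 0.5, d = 0.5, and a difference growing linearly over baseline, 2, 4 and 6 weeks: 0, 1/6, 1/3, 1/2.

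- Group main effect: mean difference 0.25; variance of a patient's four-visit mean (1 + 3 × 0.5)/4 = 0.625; noncentrality 0.25/√(2 × 0.625/36) = 1.34; power 26%.
- Group-by-time: sum of squares of the differences about their mean 0.139; λ = (36/2) × 0.139/(1 − 0.5) = 5.0 on 3 and 210 df; power 43%.
- Unadjusted week-6 contrast: 0.5/√(2/36) = 2.12; power 55%.
- Week-6 ANCOVA on baseline: residual variance 1 − ρ² = 0.75; 0.5/√(2 × 0.75/36) = 2.45; power 68%.

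**Step 3: how far this moves with ρ** (same profile, d = 0.5, 36 per arm).

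| ρ | Group main effect | Group-by-time | Unadjusted week 6 | Week-6 ANCOVA |
|---|---|---|---|---|
| 0.3 | 33% | 32% | 55% | 59% |
| 0.5 | 26% | 43% | 55% | 68% |
| 0.7 | 22% | 66% | 55% | 83% |

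**Step 4: how far it moves with the time course.** Let the effect be complete by week 2 and held, with all five visits in the ANOVA (d = 0.5, 36 per arm). The group main effect then has 71%, 58% and 48% power at ρ = 0.3, 0.5 and 0.7, against the same 59%, 68% and 83% for ANCOVA. That is a gain of 12 points at ρ = 0.3, then losses of 10 and 35.

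**Step 5: the full range.** Over d = 0.5 to 0.8, ρ = 0.3 to 0.7, 36 or 45 per arm, and gradual or immediate onset, the loss against week-6 ANCOVA is:

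- unadjusted week-6 contrast: about 1 to 28 points;
- group-by-time: about 0 to 31 points;
- group main effect: from a 12-point gain to a 64-point loss.

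**Step 6: the interaction as evidence about week 6.** Suppose the groups differ by 0.5 SD at weeks 2 and 4 only and are equal at baseline, week 6 and follow-up (ρ = 0.5, 36 per arm, five visits). The sum of squares of the differences about their mean is 0.5 − 5 × 0.2² = 0.3, so λ = 18 × 0.3/0.5 = 10.8 on 4 and 280 df. The interaction rejects 75% of the time and the group main effect 19%. A week-6 ANCOVA rejects at its nominal 5%.

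**The case against.** The strongest reply is that the protocol never commits to the weakest reading. It does not say that the group main effect is the test or that baseline is one of its levels. The total of 90 fits an interaction test, which uses baseline as its reference and does not suffer the same dilution. The LSD comparisons allow a direct look at week 6, and would show no difference there if an early effect had faded. All of this stands. A reader might infer that the plan fails to test week 6, or that it loses a fixed 20 to 45 points of power. The documents support neither: the LSD step can test week 6, and any single loss figure needs a correlation, an effect size and a time course that the protocol does not state.

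Three further replies also have force. The hypotheses name no time point, so a null hypothesis of equal means at week 6 combines them with the power sentence. The sentence naming the ANOVA covers secondary outcomes only, so for CMS the method is inferred from the sample size section. An unadjusted comparison in a randomised trial is valid: chance baseline imbalance costs precision and does not bias the comparison over repeated randomisations.

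Finally, a journal article may leave covariates to a full protocol or analysis plan. Silence on covariates alone would therefore be no finding. What remains is narrower. The article does name a method, and a better use of data already collected can replace it.

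**Conclusion.** The point holds as a free improvement. No test named in the protocol is stated to be a baseline-adjusted week-6 comparison, and the protocol does not say which of the available tests answers its week-6 aim. In the worked case (36 per arm, correlation 0.5, 0.5 SD at week 6, linear growth over four visits including baseline) every reading loses power against week-6 ANCOVA: about 41 points for the group main effect (68 − 26, before rounding), 24 for the interaction and 12 for the unadjusted week-6 contrast.

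These sizes rest on assumptions. The most favourable reading of the plan, the LSD contrast at week 6, loses between 1 and 28 points over correlations of 0.3 to 0.7. The group main effect ranges from a gain of about 12 points (effect complete by week 2, low correlation) to a loss of more than 50. The direction for the unadjusted week-6 contrast is secure whenever baseline predicts the outcome to the degree assumed here; the amount is not. Nothing here shows an inflated false-positive rate for a week-6 comparison or an invalid trial.

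**What to change.** In the Statistical analysis section, for CMS and each continuous secondary outcome:

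1. Take baseline out of the repeated factor. Use the post-baseline visits (weeks 2, 4 and 6, and the follow-up 6 weeks after treatment) as responses.
2. Fit group, visit, group-by-visit, baseline and baseline-by-visit.
3. Base the between-group conclusion on the baseline-adjusted difference at week 6 with its 95% CI. Report the other visits as supportive, and do not rest the conclusion on the overall group test or the group-by-time test.

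The cost is analysis wording and a few degrees of freedom for the baseline terms. No extra patients, visits or data are needed. SPSS 26, already named, fits the model with its MIXED procedure, or with ANCOVA for a single visit. The protocol says that amendments will be posted in the trial registry, so the change can be recorded there, preferably before any unblinded analysis.
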